# A multi-center, pragmatic, effectiveness-implementation (hybrid I) cluster randomized controlled trial to evaluate a child-oriented goal-setting approach in paediatric rehabilitation (the ENGAGE approach): a study protocol

**DOI:** 10.1186/s12887-022-03381-4

**Published:** 2022-06-29

**Keywords:** Pediatrics, Rehabilitation, Pragmatic trial, Goal-setting, Implementation evaluation

## Abstract

**Background:**

Child-oriented goal-setting in pediatric rehabilitation may improve child motivation, engagement in therapy, child outcomes related to therapy, and service delivery efficiency. The primary objective of this trial is to determine the effectiveness of a principles-driven, child-focused approach to goal-setting, Enhancing Child Engagement in Goal-Setting (ENGAGE), on pediatric rehabilitation outcomes compared to usual practice. The three secondary objectives are to 1) compare costs and secondary outcomes of the ENGAGE approach to usual practice, 2) determine the influence of child, parent and therapist characteristics on child engagement in therapy and rehabilitation outcomes, and 3) identify barriers and facilitators to the implementation of ENGAGE.

**Methods:**

This research protocol describes a pragmatic, multi-site, cluster, effectiveness-implementation (hybrid type 1 design) randomized controlled trial. Therapists (*n* = 12 clusters of two therapists) at participating sites (*n* = 6) will be randomized to 1) the ENGAGE intervention group, or 2) usual care (control) using a computer-generated, permuted-block randomization sequence with site as a stratification variable designed by a statistician (RR). Each therapist will recruit four children 5–12 years old with neurodevelopmental conditions (*n* = 96), who will receive ENGAGE or usual care, according to therapist group allocation. ENGAGE therapists will be trained to use a 'toolbox' of evidence-driven, theory-informed principles to optimize child and parent motivation, engagement in the goal-setting process, and performance feedback strategies. Outcomes include goal performance (primary outcome), engagement in therapy, functional abilities, participation, and parent and child quality of life. Qualitative interviews with children, parents, ENGAGE therapists, and managers will explore challenges to implementation and potential mitigation strategies. Mixed effects multiple linear regression models will be developed for each outcome to assess group differences adjusted for clustering. A cost-effectiveness analysis will combine cost and a measure of effectiveness into an incremental cost-effectiveness ratio. Qualitative data on implementation will be analyzed inductively (thematic analysis) and deductively using established implementation science frameworks.

**Discussion:**

This study will evaluate the effects of collaborative goal-setting in pediatric rehabilitation and inform effective implementation of child-focused goal-setting practices.

**Trial Registration:**

NCT05017363 (registered August 23, 2021 on ClinicalTrials.gov).

## Background

Many children with neurodevelopmental conditions access rehabilitation services, such as occupational therapy (OT) and physical therapy (PT), to optimize functional abilities and meaningful participation and inclusion in important life activities [1]. Thus, a focus on individualized goal setting and identifying outcomes that are meaningful to children and families is a foundational component of OT and PT intervention [2, 3]. Despite the importance of focusing therapy on activities that are meaningful to children and families, implementing individualized goal-setting in pediatric rehabilitation has been challenging [4–7]. Our previous research [6, 8–11] and work by others [3, 4, 12, 13] indicates that parent engagement in goal setting processes is suboptimal for various reasons including (1) mismatch between clinician and parent perspectives on appropriate goals, (2) lack of therapist confidence in the abilities of parents to identify meaningful goals, and (3) organizational barriers such as lack of time, challenges with service team coordination, and poor documentation. Even less emphasis is placed on ensuring children are optimally engaged in the goal setting process [13], despite evidence that perceived goal importance plays a crucial role in behavior change that leads to goal performance [14]. For example, some therapists worry that engaging a child with autism in goal-setting may perpetuate restricted interests; while parents and youth with autism perceive goals to be more meaningful when they are grounded in activities the child finds engaging [10].

Collaborative goal-setting aligns therapy with individualized goals of children and families; enacting the tenets of family-centered care. This approach is recognized as best practice with children with disabilities [12, 15]. Furthermore, engaging children in goal-setting could positively affect rehabilitation outcomes due to increased motivation to participate in goal-related therapy activities [13, 16], particularly since children as young as five are capable of identifying achievable goals [17, 18]. Collaborative goal-setting may also improve service delivery efficiency by providing more targeted interventions [4].

To evaluate the effects of child-focused goal setting on outcomes and service delivery efficiency, we have developed the Enhancing Child Engagement in Goal Setting (ENGAGE) approach**.** ENGAGE operationalizes principles of relevant theoretical frameworks [13, 19], contemporary approaches to rehabilitation emphasizing individualized goals [20, 21], and the evidence supporting children’s ability to engage in goal setting [18]. ENGAGE aims to ensure that children have a voice by optimizing their involvement in goal-setting and encouraging clinical judgment in tailoring the use of tools and strategies to children and families’ needs. There is evidence that prescriptive, one-size-fits-all approaches have resulted in disappointing uptake elsewhere [3]. In addition, variability in parenting styles, such as the extent to which a parent is comfortable with adult versus child-directed decision-making, should be considered in child-focused approaches to rehabilitation goal-setting. See Fig. 1 for the ENGAGE study theoretical framework.

**Fig. 1 Fig1:**
[figure not shown]
Study conceptual model (moderators indicated with thin arrows)

It is well established that integrating new, evidence-informed approaches, including goal-setting approaches, into daily practice is incredibly challenging [22]. Process, intervention characteristics, people influences, and context of an intervention, rather than evidence for its effectiveness, can play a more critical role in its successful adoption and widespread use [23]. Therefore, an important component of facilitating uptake of a new approach is identifying and understanding barriers and facilitators to implementation to guide the development of targeted implementation strategies [24–26]. Implementation evaluations are crucial for closing research to practice gaps and have influenced significant practice changes in other areas of health care [27].

The primary clinical effectiveness trial objective is to determine the effectiveness of a collaborative goal-setting approach on therapists’ perception of child engagement in therapy, goal performance (primary outcome), functional abilities, participation in home, school and/or community, and child and caregiver quality of life compared to usual practice. The secondary effectiveness evaluation objectives are: 1) to assess the incremental cost of ENGAGE compared to usual care relative to the study outcomes, and 2) to determine the influence of child, parent, and therapist characteristics on child engagement and outcomes.

The implementation evaluation objectives are: 1) to identify barriers and facilitators to implementation of ENGAGE, such as clinical contexts, child and family characteristics, and specific features of ENGAGE, 2) to understand family and therapist perspectives on the key components of ENGAGE that are associated with perceived effectiveness, and 3) to determine if differences are present in barriers and facilitators to implementation in rural and urban pediatric rehabilitation sites, and in different types of programs.

## Methods/design

### Study setting

The study will be conducted in six established pediatric rehabilitation sites in rural and urban settings in Alberta, Canada. Goal-setting and intervention can occur in a variety of settings (e.g., clinic, family home). The study opened to enrolment in February 2022.

### Trial design

This is a pragmatic, cluster randomized controlled trial (RCT) with therapists randomized to one of two groups; the ENGAGE intervention group or the usual care control group. The RCT will be a six-site trial with two groups (ENGAGE training absent/present) with two periods of post-intervention assessment (immediate post-treatment and three-month follow-up). Core features of a pragmatic design include a comparison of clinically feasible and relevant interventions, the inclusion of diverse patient populations and practice settings, and the measurement of a broad range of outcomes [28]. This trial can also be categorized as a Hybrid Type 1 design [29], a clinical intervention coupled with observing implementation with intent to inform scale and spread. The methodology specific to the clinical effectiveness trial will be described separately from the implementation evaluation. A cost-effectiveness analysis will also be conducted in conjunction with the RCT.

### Clinical effectiveness trial methodology

#### Eligibility criteria

Consistent with eligibility determination recommended for pragmatic trials [30], inclusion criteria are broad and exclusion criteria are minimal. Inclusion criteria are children who: 1) are 5–12 years old, 2) are referred to PT and/or OT for a period of direct treatment, 3) are able to engage in the goal-setting process by communicating verbally or non-verbally (based on therapist clinical judgment), and 4) understand English. Children will be excluded from the trial if 1) the parent or guardian who attends therapy does not speak English, 2) the child has a diagnosis associated with developmental/neurological regression, such as uncontrolled seizures.

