### Sample size

The sample size will be 96 children (12 therapists as clusters per group and four children per therapist) recruited from the six separate sites by the study therapists (4 children/therapist). Based on our pilot work, we anticipate that child dropout from the pre-post intervention period will be minimal (i.e., less than 5%). A target change score of 2.0, a clinically significant change on the Canadian Occupational Performance Measure (goal performance rating) (COPM-P; primary outcome) [31], with a standard deviation of 2.75 [32] corresponds to an effect size of 0.723 for the comparison of means. A sample size of 96 will enable us to detect an effect size of at least 0.682 in the primary outcome (alpha = 0.05 and 80% power), assuming an intra-cluster correlation (ICC) of 0.1 using a 2-sided, cluster-adjusted, t-test for the comparison of means. We selected an ICC of 0.1 based on the results of a previous cluster RCT with children with cerebral palsy (ICCs between 0.08 to 0.13) [32]. Since therapist attrition is possible over the duration of the study, a cluster size of 11 would still provide 80% power to detect an effect size of 0.716, below our target effect size. Smaller effect sizes will be detectable if the ICC is smaller than 0.1.

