### Consent and confidentiality

All parents will sign an informed consent document and children nine years of age and older will sign an assent form. Forms will be provided to the families by study therapists and returned directly to the study investigators. All data will be stored separately from identifiers on a password-protected, secure server at the University of Alberta. Only the list authors will have access to the trial dataset.

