### Randomization

A computer-generated, permuted-block randomization sequence stratified by site will be used to allocate 24 OTs and PTs across six sites to ENGAGE or usual care to ensure balanced groups. Blocked randomization by site will facilitate consistency of therapy interventions and child characteristics between groups with the exception of ENGAGE in the intervention. If therapists within more than one program per site participate, therapists will also be randomized by program. The randomization sequence will be uploaded to Research Electronic Data Capture (REDCap) [33] to allow centralized, online randomization. Randomization of therapists (and not children) will decrease contamination in the usual practice group (i.e., so therapists are not asked to go between intervention and usual care practices). Blocked randomization by site will facilitate equal group distribution related to therapy interventions (e.g., types of therapy) and child characteristics (e.g., age, diagnosis). See Fig. 2 for the Consolidated Standards of Reporting Trials (CONSORT) study flowchart.

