### Fidelity monitoring

Following the training, we will track the strategies used by both groups of therapists to evaluate treatment fidelity prior to recruiting participants to ensure 1) that therapists in the ENGAGE group are adhering to intervention principles, and 2) that the practices in the two groups are different. Recruitment and formalized data collection will begin once intervention-group therapists at the site achieve an acceptable level of fidelity defined as adherence to ENGAGE principles and group practices are established to be different, or repeated attempts to support therapist in using the ENGAGE approach have been exhausted. Intervention-group therapists will self-report their adherence to ENGAGE principles using a Likert scale. For example, they will report on the extent to which children are involved in identifying their own goals and their use of feedback on goal-related performance at each treatment session. Practices in the control group will be tracked using a form with open-ended questions to prevent contamination from exposure to ENGAGE principles. Ongoing documentation of practices and monitoring will be used to evaluate the need for additional or different implementation support in the intervention group. Co-interventions will be monitored bi-weekly.

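### Children are recruited, and one eligibility criterion is judged, by the randomised therapists after allocation and after ENGAGE training, so the arms can differ through selection.

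*Protocol article*

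**What the plan says.** The sequence has to be put together from several sections of the protocol article.

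- **Allocation.** Under Randomization, a sequence stratified by site "will be used to allocate 24 OTs and PTs across six sites to ENGAGE or usual care".
- **Training.** Under Treatments, ENGAGE therapists receive manualised training in child engagement and goal-setting. Control therapists receive no training in child engagement strategies.
- **Run-in.** Under Fidelity monitoring, after training, "we will track the strategies used by both groups of therapists to evaluate treatment fidelity prior to recruiting participants". Then: "Recruitment and formalized data collection will begin once intervention-group therapists at the site achieve an acceptable level of fidelity", or once attempts to support the therapist are exhausted.
- **Recruitment.** The abstract says "Each therapist will recruit four children", and Sample size says the children are "recruited from the six separate sites by the study therapists (4 children/therapist".
- **Consent.** "Forms will be provided to the families by study therapists and returned directly to the study investigators".
- **Eligibility.** The third inclusion criterion is that children "are able to engage in the goal-setting process by communicating verbally or non-verbally (based on therapist clinical judgment").
- **Masking.** Under Blinding, assessors and the statistician are masked. Therapists are not listed, and families cannot be masked.
- **Stated safeguard.** Under Randomization: "Blocked randomization by site will facilitate equal group distribution related to therapy interventions (e.g., types of therapy) and child characteristics", with age and diagnosis as examples. Treatments adds that pairing within programs makes similar populations more likely.

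**The concern.** In a cluster trial, randomisation protects the comparison of clusters. It protects the comparison of individuals only if their entry does not depend on the allocation. Here the person who identifies, assesses and approaches each child is the person who was randomised. That person acts after allocation and, in one arm only, after training in how to engage children in goal-setting.

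Criterion 3 makes this sharper. It asks for a clinical judgement on whether a child can take part in goal-setting. A trained therapist may see that ability in children whom an untrained colleague would regard as unable, or may favour children likely to respond. Either could happen in good faith, and they push in opposite directions.

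At stake is the validity of the COPM-P comparison. Masked assessment protects measurement, not enrolment. The ICC allowance in the sample size deals with variance, not bias.

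**Working it through.** **1. Order of events.** Therapists randomised (Randomization); ENGAGE arm trained (Treatments); practices tracked in both arms (Fidelity monitoring); recruitment opens at the site (Fidelity monitoring); therapists recruit, judge criterion 3 and hand out consent forms (abstract, Sample size, Eligibility criteria, Consent and confidentiality). Every step that decides which children enter follows allocation.

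**2. What each safeguard reaches.**
- Stratifying by site and program, and pairing within programs, make the two arms' therapists and referral streams alike. They do not act on which referrals are enrolled.
- The mixed models with covariates (Statistical analysis) act on measured child characteristics only. The primary analysis is a cluster-adjusted t-test of COPM-P change, for which no covariates are named.
- Masked assessors and statistician act after enrolment.

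**3. The plan's own precision.** Inputs from Sample size: 12 therapists per arm, 4 children each (48 per arm), ICC 0.1, two-sided alpha 0.05, 80% power, SD 2.75.
- Design effect = 1 + (4 − 1) × 0.1 = 1.3.
- SE of the difference in SD units = √(2 × 1.3 / 48) = 0.2327.
- Degrees of freedom = 2 × (12 − 1) = 22.
- With the noncentral t, power at an effect of 0.682 is 0.7997, which reproduces the stated detectable effect. With 11 clusters per arm (df 20, SE = √(2 × 1.3 / 44) = 0.2431), power at 0.716 is 0.800, which reproduces the second stated figure.

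The sample-size arithmetic is not in dispute. It supplies the SE used below.

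**4. Illustration of what selection could do.** The shift *b* is an assumption; no value is in the document. With no true effect, the two-sided rejection probability is P(|T| > 2.074), where T is noncentral t with 22 df and noncentrality *b* / 0.2327.

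| Shift in mean COPM-P change (SD) | COPM-P points (× 2.75) | Noncentrality | Rejection |
|---|---|---|---|
| 0 | 0 | 0 | 5.0% |
| 0.1 | 0.28 | 0.43 | 7.0% |
| 0.2 | 0.55 | 0.86 | 13.0% |
| 0.3 | 0.83 | 1.29 | 23.4% |

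**5. If the shift is in a trait, not in the change score.** A shift in a prognostic trait carries over to change in proportion to its correlation with change (also assumed).

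| Trait shift (SD) | Correlation 0.3: shift in change, rejection | Correlation 0.5: shift in change, rejection |
|---|---|---|
| 0.1 | 0.03, 5.2% | 0.05, 5.5% |
| 0.2 | 0.06, 5.7% | 0.10, 7.0% |
| 0.3 | 0.09, 6.6% | 0.15, 9.5% |

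**The case against.** **The article does not say that therapists hand-pick children.** A reader might infer free choice from the caseload. The text says only that therapists recruit four each. The order of approach and any screening log may be in the full protocol, which is not shown, and their absence from an article is not an error. This stands. The point rests on what is stated: who recruits, when, and who judges criterion 3.

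**Criterion 3 may be a low bar.** It accepts verbal or non-verbal communication, and the criteria are introduced as broad. It also concerns the child, whereas training changes the therapist. This limits the likely size of any difference, but the threshold is still set by a judgement that only one arm has been trained around.

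**The Randomization section does not promise balance.** A reader might call its statement on child characteristics false. It says only that blocking will help, and similar referral streams do help. The statement needs qualifying, not withdrawing.

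**Imbalance is acknowledged.** Statistical analysis plans models for variables that may be unbalanced, including cognitive ability, which is close to the trait at issue. That is a partial answer, but it is confined to measured factors and lies outside the primary comparison.

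**Control therapists' awareness of their allocation is inferred.** It is not stated. The mechanism does not depend on it, because a changed judgement in the trained arm alone is enough.

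**Conclusion.** The concern holds as a risk built into the stated sequence. Entry to the trial is decided after allocation by the randomised therapists, partly on a judgement in the domain of the intervention. None of the stated safeguards removes the resulting selection from the primary analysis.

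The document does not show that such bias will occur, that it would favour ENGAGE, or how large it would be. A reader might take 23% as the trial's false-positive rate. It is the result of an assumed 0.3 SD shift in the change score itself. Over the assumed shifts of 0.1 to 0.3 SD, rejection under no effect runs from about 7% to 23% if the shift is in change, and from about 5% to 9.5% if it is in a trait correlated 0.3 to 0.5 with change. These figures rest on the plan's ICC of 0.1, 22 df and full enrolment. The remedy is a cheap improvement and leaves the sample size as it is.

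**What to change.** For the recruitment that remains:

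1. Offer the study to each therapist's eligible referrals in date order until four children are enrolled.
2. Judge criterion 3 by one written rule, applied identically in both arms, from referral or intake information.
3. Log every child not offered the study or declining it, with the reason. Report these counts and the baseline characteristics by arm, and by whether enrolment was before or after the change.
4. Qualify the Randomization section: blocking and pairing make therapists and referral streams comparable, but do not assure comparable children when children enter after allocation.

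**Cost.** Study setting gives February 2022 as the opening of enrolment, so this is a mid-trial amendment that leaves children recruited under two rules. It also needs a short screening log per therapist and may slow recruitment slightly. It needs no extra staff. It does not remove differential consent, since families cannot be masked and receive the forms from the study therapists.

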### Sample size

The sample size will be 96 children (12 therapists as clusters per group and four children per therapist) recruited from the six separate sites by the study therapists (4 children/therapist). Based on our pilot work, we anticipate that child dropout from the pre-post intervention period will be minimal (i.e., less than 5%). A target change score of 2.0, a clinically significant change on the Canadian Occupational Performance Measure (goal performance rating) (COPM-P; primary outcome) [31], with a standard deviation of 2.75 [32] corresponds to an effect size of 0.723 for the comparison of means. A sample size of 96 will enable us to detect an effect size of at least 0.682 in the primary outcome (alpha = 0.05 and 80% power), assuming an intra-cluster correlation (ICC) of 0.1 using a 2-sided, cluster-adjusted, t-test for the comparison of means. We selected an ICC of 0.1 based on the results of a previous cluster RCT with children with cerebral palsy (ICCs between 0.08 to 0.13) [32]. Since therapist attrition is possible over the duration of the study, a cluster size of 11 would still provide 80% power to detect an effect size of 0.716, below our target effect size. Smaller effect sizes will be detectable if the ICC is smaller than 0.1.

